### Intervention

Eligible patients will be enrolled following a consultation with an investigator, after checking that they meet the inclusion and exclusion criteria (and signing an informed consent).

The specific needs of the study are to provide a biological sample and to assess individual frailty and quality of life longitudinally.

Blood samples will be collected at diagnosis, 3 months and 12 months after treatment initiation. Optionally, a bone marrow sample taken at diagnosis will be retained. This will be used to compare the BA between the blood and bone marrow compartments.

An assessment of individual frailty and quality of life will be performed at diagnosis, 6 months after treatment initiation, and then annually for 3 years.

Pseudonymized blood samples will be stored by every sites and then sent to the CRB-Auvergne (France) for analysis. Blood samples will be analyzed to assess BA.

The risks or constraints for subjects participating in the study appear to be minimal, as the only intervention is blood tests.

### Determination of biological age and evaluation of individual frailty

DNA methylation profile analysis is currently the most robust method for assessing BA. DNA methylation clocks mainly use data from HM450K chips (Illumina), which cover the majority of CpG islands. However, these have been replaced by the recently validated EPIC BeadChip kit, despite the loss of some targets [16]. Based on the results obtained with the EPIC BeadChip kit, BA will be determined using the Horvath [10], Hannum [7] and DNAmPhenoAge [8] algorithms, which combine the methylation profile and certain biological assays. In addition, next generation sequencing will be performed to assess the presence of mutations of CHIP and measurement of telomere length will be carried out.

These analyses will be carried out at the time of diagnosis, prior to any treatment, in order to characterise the DNA methylation profile of malignant cells. They will also be carried out 3 months and 12 months after the start of treatment, when the residual BCR::ABL1/ABL1 transcript is low. This will enable the DNA methylation profile of non-malignant cells to be described.

Individual frailty will be assessed using the Rockwood score [17] and the G-CODE questionnaire [18]. The Rockwood score is a measure of frailty based on clinical judgement. The scale ranges from 1 (very good physical condition) through 7 (complete functional dependence) to 9 (at the end of life). The rise of one category on the scale significantly increases the risk, in the medium term, of death and admission to a health establishment. The scale is simple to use and can be easily administered in a clinical setting, enabling care to be adapted and communication with the patient or the various clinical staff to be adapted. The G-CODE defines the minimum geriatric information to be collected at the time of inclusion of patients in clinical trials. It is used to describe elderly cancer patients and to standardise the collection of geriatric data in therapeutic trials but could be applied to younger patients. It consists of the following 7 parts: Social assessment: living alone or support requested to stay at home; Functional autonomy: Activities of Daily Living questionnaire and short Instrumental Activities of Daily living questionnaire; Mobility: Timed Up and Go test; Nutrition: weight loss during the past 6 months and body mass index; Cognition: Mini-Cog test; Mood: mini-Geriatric Depression Scale; Comorbidity: updated Charlson Comorbidity Index.

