### Study objectives and endpoints

#### Main objective and endpoint

The main objective of the study is to evaluate the value of combining BA determination with individual fragility assessment to personalize the management of CML patients treated with TKI, in terms of tolerances.

The first primary endpoint is the difference between BA and chronological age (of the CML clone and non-malignant cells in the same patient) expressed as a difference and as a percentage (ratio).

The second endpoint is the individual frailty assessed using G-CODE score, Rockwood Frailty Scale and Charlson Comorbidity Index.

And the last endpoint is the TKI tolerance in patients with CML assessed by actual dose received, TKI discontinuation due to intolerance, TKI discontinuation due to adverse events, TKI changes due to intolerance and number of TKI lines.

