### Data analysis

Continuous data will be expressed using mean and standard deviation or median and interquartile range, according to their statistical distribution. The normality assumption will be studied using the Shapiro-Wilk test.

The relationship between chronological age and BA will be investigated using correlation and concordance coefficients (Lin for continuous data and Cohen’s kappa for categorical data), Bland and Altman plot and approaches based on non-linearity assumptions. The difference between BA and chronological age will be expressed as a difference and as a percentage (ratio) to assess the relevance of these two modalities.

The relationship between BA, difference between BA and chronological age and frailty will be analyzed using correlation coefficients (Pearson or Spearman, depending on the statistical distribution) and mediation analysis.

A detailed description of frailty will be carried out. First, frailty will be treated as an ordinal variable. Then, frailty will be categorized according to statistical distribution and to data reported in the literature. Likewise, age (BA and chronological age) will be considered as a continuous variable and then as a categorical variable with groups defined according to their clinical relevance and statistical distribution. The relationships will be analyzed using the Chi-square test or Fisher’s exact test (categorical x categorical) and the analysis of variance or Kruskal-Wallis test if the assumptions of the analysis of variance are not met (categorical x continuous).

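### Raw BA-minus-age difference and ratio, from clocks run on a newer array with admitted target loss, could mix platform shift with ageing and pick up chronological age

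*Protocol article*

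**What the plan says.** In the protocol article, the section on determination of biological age says "DNA methylation clocks mainly use data from HM450K chips (Illumina), which cover the majority of CpG islands" and that "these have been replaced by the recently validated EPIC BeadChip kit, despite the loss of some targets". Three published clocks are then applied to EPIC results.

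Under Main objective and endpoint: "The first primary endpoint is the difference between BA and chronological age (of the CML clone and non-malignant cells in the same patient"), and this is to be "expressed as a difference and as a percentage (ratio"). Data analysis repeats both forms and says their relevance will be compared. It examines BA against chronological age with "correlation and concordance coefficients (Lin for continuous data and Cohen’s kappa for categorical data), Bland and Altman plot". BA, the difference and "frailty will be analyzed using correlation coefficients (Pearson or Spearman, depending on the statistical distribution) and mediation analysis". Mixed, Cox and joint models follow. Age appears among the example confounders for the tolerance and response models.

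Eligibility (Table 1) admits only newly diagnosed chronic-phase CML, and the sampling described is from those patients alone.

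**The concern.** A methylation clock is a score built over a set of sites. If a clock is run on an array that lacks some of its sites, BA may move by a number of years (level), or rise by more or less than one year per year of age (slope), while still ranking patients well. A correlation with age would hardly show this. A raw difference, a ratio, a Bland-Altman bias and Lin's coefficient all depend on the absolute scale.

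Two things are at stake. First, with no unaffected samples on the same array, a mean BA-minus-age different from zero is the sum of platform shift and biology, and the described data cannot separate them. Second, a level shift makes the ratio vary with chronological age, and a slope other than 1 does the same to the difference. Frailty also tends to rise with age, so an unadjusted correlation of either form with frailty could reflect age alone.

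**Working it through.** **Nearest stated figure.** Sample size: 200 patients, 45% frail or pre-frail (90 versus 110), effect size 0.5, two-sided alpha 0.01. Power = Φ(0.5 × √(90 × 110 / 200) − 2.576) = Φ(3.518 − 2.576) = Φ(0.942) = 82.7%, which agrees with the stated power above 80%. A constant offset in BA cancels from this comparison.

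**Assumptions (none is in the documents).** Chronological age N(58, 16) truncated to 18–90, which leaves an SD of about 14.7; SD of BA minus age 5 years; no true acceleration; frailty correlates 0.5 with age and not at all with BA given age; n = 321. Offsets c of 2, 3 and 5 years, or slope 0.95, illustrate the range.

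**Formulas.**
- Mean difference and Bland-Altman bias = c.
- Share with BA above age = Φ(c/5).
- Lin's coefficient = 2 × 14.7² / (2 × 14.7² + 25 + c²).
- Error in the ratio = c / age.
- Ratio-frailty correlation = 0.5 × ratio-age correlation (the latter simulated).
- Rejection at 5%: Fisher z, √318 × atanh(r), against 1.96.

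| | c = 0 | c = 2 | c = 3 | c = 5 |
|---|---|---|---|---|
| Bland-Altman bias (years) | 0 | 2 | 3 | 5 |
| Share with BA above age | 50% | 66% | 73% | 84% |
| Lin's coefficient | 0.945 | 0.937 | 0.927 | 0.896 |
| Error in ratio at age 30 | 0 | 6.7% | 10% | 16.7% |
| Error in ratio at age 80 | 0 | 2.5% | 3.8% | 6.3% |
| Ratio-age correlation | 0 | −0.11 | −0.17 | −0.27 |
| Ratio-frailty correlation | 0 | −0.06 | −0.09 | −0.14 |
| False rejection, ratio v. frailty | 5% | 17% | 33% | 69% |
| False rejection, difference v. frailty | 5% | 5% | 5% | 5% |

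Negative offsets give the mirror image.

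**Slope 0.95, no mean shift.** The difference is −0.05 × (age − mean) plus scatter. Its correlation with age is −0.05 × 14.7 / √((0.05 × 14.7)² + 25) = −0.735 / 5.054 = −0.145. With frailty it is 0.5 × −0.145 = −0.073. Then √318 × 0.073 = 1.30, and rejection is P(Z > 1.96 − 1.30), about 26%.

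**Age-adjusted measure.** The residual of BA on chronological age has zero correlation with age whatever the level or slope, so it has no age route to frailty, and false rejection stays at no more than 5%. Chronological age as a covariate does the same job.

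**What a constant offset does not touch.** In a second simulation (age about 55, SD 15, scatter SD 5, frailty truly related to acceleration), the difference-frailty correlation is 0.448 at every offset from −6 to +6 years. The ratio-frailty correlation falls from 0.423 to 0.419 at +2 and 0.409 at +4. For clone versus non-malignant cells in one patient, (BA₁ + c − age₁) − (BA₂ + c − age₂) no longer contains c.

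**The case against.** The strongest reply is that no shift is shown. The article calls the kit validated, does not say that the lost targets belong to any of the three clocks, and gives no size. Handling of absent sites and normalisation can properly sit in a laboratory manual, full protocol or analysis plan. All of that stands: the absence of a calibration step from an article is no finding, and the figures above are conditional.

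Second, most planned analyses are associations, and a constant offset drops out of those that use BA or the difference. That also stands. A reader might infer that the main objective on tolerance is compromised; on the difference scale with a constant offset it is not.

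Third, no test of the mean difference against zero is planned, the two forms of the endpoint will be compared, and age is a listed confounder for tolerance and response. This stands in part. The agreement statistics are still planned outputs that invite a reading as acceleration. The frailty relationship is first described as plain correlations. Comparing the two forms does not help if one of them carries age by construction.

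Fourth, any constant shift, real acceleration included, makes the ratio depend on age. True, and it is a further reason not to carry inference on the ratio.

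**Conclusion.** The point holds in conditional form. What the article itself fixes is the form of the endpoint (raw difference and ratio) and the agreement statistics, in a design with no described reference samples and an acknowledged loss of targets. A platform shift in level could be mistaken for accelerated or slowed ageing in the mean difference, the Bland-Altman bias and Lin's coefficient. A level shift makes the ratio age-dependent, and a slope other than 1 does so for the difference.

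Under the assumptions stated, false ratio-frailty findings occur in about 17%, 33% and 69% of studies at offsets of 2, 3 and 5 years, and false difference-frailty findings in about 26% at slope 0.95, against 5% nominal. These rates depend on the assumed offset, slope and age-frailty correlation.

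A reader might go further and conclude that an array artefact will be reported as ageing. The documents do not support that, since they neither state a shift nor place the lost targets within the clocks.

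**What to change.** Amend Main objective and endpoint and Data analysis as follows.

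1. For each clock, base the frailty and tolerance associations on an age-adjusted measure: either the residual of BA regressed on chronological age in all study samples of the same time point, or BA with chronological age as a covariate.
2. Keep the raw difference for the within-patient clone versus non-malignant contrast. Residuals formed per time point average zero at each time point and cannot show that contrast.
3. Make the ratio descriptive.
4. State that the uncalibrated mean difference, Bland-Altman bias and Lin's coefficient will not be read as evidence of accelerated ageing.

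Do not calibrate on the month-12 low-transcript samples alone. That selects patients on response, which is a secondary outcome, and forces mean acceleration in non-malignant cells to zero, although those cells are part of the first primary endpoint.

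The cost is a few sentences and one regression per clock and time point, on data already planned. The study gives up a claim about the absolute mean level of acceleration, which the described design cannot support without unaffected samples on the same array.

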### Study procedures and participant timeline

The overview of study assessments and procedures are presented in Table 2.

**Table 2 Tab2:** Data collection schedule

	DIAGNOSTIC	ACTIVE TREATMENT PHASE				
	INCLUSION	M3 *(+/- 8 days)*	M6 *(+/- 8 days)*	M12 *(+/- 10 days)*	M24 *(+/- 10 days)*	M36 *(+/- 10 days)*
Information and consent	X					
**Clinical evaluation**						
Medical history and current comorbidities	X					
History of the disease	X					
Weight and height (BMI calculation)	X	X	X	X	X	X
Rockwood score **	X		X	X	X	X
EORTC QLQ C30	X		X	X	X	X
G-CODE	X		X	X	X	X
Treatment tolerance		X	X	X	X	X
**Biological evaluation**						
Biological collection (blood)	X	X		X		
Optional biological collection (marrow)	X					
Albumin, C-reactive protein, creatinine, creatinine clearance*, hemoglobin	X	X	X	X	X	X
**Tumor evaluation**						
Evaluation of tumor response (hematological, cytogenetic, molecular, plasma assay, BCR::ABL mutation when tested)		X	X	X	X	X

*According to the Cockroft-Gault formula and the CKD-EPI equation

**If carried out by a clinical research associate or a nurse, the assessment must be validated by a geriatrician

### Sample size

The sample size in order to study the relationship between BA, individual frailty and tolerance to TKIs will be estimated according to Hanlon P. et al. [19], Huan-Tze L. et al. [20] and the data from CML Observatory.

Considering 45% frail and pre-frail patients, an effect size greater than 0.5 (moderate to large according to Cohen’s rules of thumb) between BA and individual frailty can be highlighted with 200 patients, for a two-sided type I error at 0.01 (correction due to multiple comparisons) and statistical power above 80%. An interim analysis is planned at inclusion of 100 patients to estimate statistical power according to observed effect sizes and 95% confidence intervals.

Furthermore, given the data reported in the literature [21] and data from CML Observatory, it seems reasonable to expect 35% TKI intolerance. Thus, an enrolment of 321 patients will enable us to identify a 15% absolute difference in intolerance (treated as censored data) for a two-sided type I error of 5% and statistical power of 80%, which correspond to a reasonable hazard ratio of at least 1.4.

An interim analysis is planned at inclusion of 100 patients to re-estimate statistical power according to observed effect sizes and 95% confidence intervals for the relationship between BA and individual frailty.

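### The single 80% power for intolerance counts every event from treatment start, but non-malignant biological age is first available at M3, so its power is below 80%

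*Protocol article*

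**What the plan says.** The Sample size section of the Protocol article opens with its purpose: "The sample size in order to study the relationship between BA, individual frailty and tolerance to TKIs". For tolerance it states that "it seems reasonable to expect 35% TKI intolerance" and that "an enrolment of 321 patients will enable us to identify a 15% absolute difference in intolerance (treated as censored data"), at two-sided 5% and 80% power. It adds of this difference: "which correspond to a reasonable hazard ratio of at least 1.4". It names neither the groups compared, nor the time origin, nor the horizon of the 35%.

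Under Main objective and endpoint, the first primary endpoint is the gap between BA and chronological age "of the CML clone and non-malignant cells in the same patient".

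The section on determining biological age assigns the pre-treatment sample to malignant cells. Of the analyses that describe non-malignant cells it says: "They will also be carried out 3 months and 12 months after the start of treatment". Table 2 agrees: blood is collected at inclusion, M3 and M12 only, while treatment tolerance is already recorded at M3. The Data analysis section relates BA to tolerance through a marginal Cox model with time-dependent variables and through joint models.

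**The concern.** One power figure is offered for a family of predictors that become known at different times. Frailty and the diagnosis BA exist when treatment starts. Non-malignant BA does not exist before M3. In a Cox model with time-dependent covariates, each event compares the covariate of the patient who has it with the covariates of those still at risk. At an event before M3 there is no non-malignant value to compare. Carrying the M3 value back to treatment start would use information from the future, taken after treatment has acted.

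Events before M3 therefore count towards the stated 80% but not towards the precision of this predictor. A reader of the Sample size section would take a null result for non-malignant BA to come from an analysis with 80% power, when that power was not available for it.

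**Working it through.** **Inputs from the documents:** N = 321, intolerance 35%, difference 15 points, two-sided alpha 5%, power 80%, follow-up 3 years, non-malignant samples at M3 and M12.

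**Assumptions:** the 35% is reached at 36 months; groups are of equal size; event times follow a Weibull with shape k = 1 (constant hazard) or k = 0.6 (early-loaded). The documents give no event timing.

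**Two readings of the 35%**
- Reading A, 35% overall (27.5% against 42.5%): HR = ln(0.575)/ln(0.725) = 1.721; events 321 × 0.35 = 112.
- Reading B, 35% in the lower group (35% against 50%, 42.5% overall): HR = ln(0.50)/ln(0.65) = 1.609; events 321 × 0.425 = 136.

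**Step 1: reproduce the plan's figure**
- A, Freedman: 112 events / 0.35 = 320 patients.
- B, Schoenfeld: 139 events / 0.425 = 327 patients.
- Schoenfeld power, Φ(ln HR × √(E × 0.25) − 1.96), with all events: A, 0.543 × √28.1 − 1.96 = 0.92, so 82%; B, 0.476 × √34.1 − 1.96 = 0.82, so 79%.

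The figure of 321 with 80% is reproduced with every event counted. If pre-M3 events were set aside under a constant hazard, the same methods would need 112 / (0.35 × 0.899) = 356 patients (A) or 139 / (0.425 × 0.894) = 366 (B). The plan therefore made no such allowance.

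**Step 2: share of events before the sample**
Share before month t = [1 − exp(−H × (t/36)^k)] / P, with H = −ln(1 − P). For A, P = 0.35 and H = 0.431; for B, P = 0.425 and H = 0.553. Example, A at M3 with k = 1: (1 − exp(−0.0359)) / 0.35 = 10.1%.

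**Step 3: power from the remaining events**
The detectable HR at 80% power is exp(2.80 / √(E × 0.25)).

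| Value used from | Hazard | Events before (A / B) | Events left (A / B) | Power (A / B) | Detectable HR (A / B) |
|---|---|---|---|---|---|
| Treatment start | any | 0 | 112 / 136 | 82% / 79% | 1.70 / 1.62 |
| M3 | constant | 10% / 11% | 101 / 122 | 78% / 75% | 1.75 / 1.66 |
| M3 | shape 0.6 | 26% / 28% | 83 / 99 | 69% / 66% | 1.85 / 1.76 |
| M12 only | constant | 38% / 40% | 69 / 82 | 62% / 58% | 1.96 / 1.85 |
| M12 only | shape 0.6 | 57% / 59% | 48 / 57 | 47% / 43% | 2.24 / 2.11 |

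A 45/55 split, borrowed from the section's frailty calculation, lowers each power by about half a point or less and raises the largest M3 detectable HR to 1.86.

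**Step 4: the hazard ratio of 1.4**
A 15-point difference corresponds to an HR of 1.6 to 1.7. The ratio 50/35 = 1.43 is a risk ratio. At HR 1.4, even with all events, power is 43% (112 events) to 50% (136 events), so the 80% cannot be attached to that value for any predictor.

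**The case against.** The strongest reply is that the Sample size section contains no arithmetic error here. It never says that its 80% belongs to non-malignant BA. The 15-point difference may be between frailty groups or diagnosis-BA groups, both known at treatment start, and for those the timing of samples costs nothing. That stands, and it is why the remedy is to name the predictor and not to enlarge the study.

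A reader might infer that power is as low as 43-47%. The documents do not support this: the section on determining biological age treats M3 as well as M12 as a time when residual transcript is low. A time-dependent covariate would enter at M3 and be updated at M12, so only pre-M3 events are lost. The M12 rows apply only if the M3 sample proves unusable.

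Nor is it certain that patients with early events contribute nothing. Intolerance does not end follow-up, TKI changes and number of lines are themselves outcomes, and a marginal model may use repeated events. Joint models might also recover part of the loss. These routes stand as possibilities, but they need modelling assumptions that the stated calculation does not contain.

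Two further inferences go too far. No section ranks non-malignant BA above the clone's BA as a predictor of tolerance. And since the Data analysis section promises effect sizes with 95% confidence intervals, imprecision in a null result would be visible to a careful reader.

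**Conclusion.** The point holds in a limited form. The stated 80% is sound for a 15-point difference in a predictor known at treatment start, but it is not delivered for non-malignant BA, which is part of the first primary endpoint. With the M3 value, power is about 75-78% under a constant hazard, a loss of 4 to 5 points from the full-event figure. It is about 66-69% under the early-loaded hazard, a loss of about 13 to 14 points.

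The direction follows from the documents whenever any event precedes M3. The size rests on the assumed 3-year horizon, the group sizes and above all the event timing, none of which is given. The range is not a bound: a steeper early hazard (shape 0.5), scaled from 80%, gives about 62-63% from M3.

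**What to change.** In the Sample size section:
1. State which predictor, which groups and which time origin the 80% refers to, and the horizon of the 35%.
2. Limit the 80% to predictors known at treatment start, for a 15-point difference expressed as HR about 1.6 to 1.7, and remove the equation with 1.4.
3. Give a separate power or detectable HR for non-malignant BA that counts only events after its sample, with the timing assumption written beside it. On the assumptions above the detectable HR from M3 is about 1.66 to 1.86. The CML Observatory, already cited in that section as a data source, may be able to supply the observed timing.

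The cost is a change of wording and one less favourable stated figure. No patients, visits or samples are added.

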For longitudinal analyses, mixed models will be used to analyze the relationship between BA, difference between BA and chronological age, and temporal changes of level of frailty, taking into account between and within patient variability (patient as random-effect). The evolution of frailty will be also assessed by trajectory modelling. The relationship between trajectories and the difference between BA and chronological age will be analyzed using analysis of variance or Kruskal-Wallis test. Multivariate analyses will be carried out to take into account confounding factors selected according to univariate results and to their clinical relevance. A particular attention will be paid to multicollinearity. Center will be considered as random-effect. The results will be expressed with effect sizes and 95% confidence intervals. Sensitivity analyses will be proposed in order to study the statistical nature of the missing data and to propose the most appropriate imputation method.

The relationships between BA, difference between BA and chronological age, individual frailty and quality of life will also be investigated.

Tolerance criteria (actual dose received, discontinuation of TKI due to intolerance, adverse events, TKI changes and number of TKI lines) will be the subject of detailed descriptive analysis. Then, marginal Cox model with time-dependent variables and joint models for longitudinal data will be used to analyze the impact of BA, difference between BA and chronological age, and individual frailty on tolerance to TKIs and therapeutic response. The proportional hazards hypothesis will be tested using the Schoenfeld test and residual plot. Death will be treated as a competitive risk using Fine and Gray model. Multivariate analyses will be performed to take account of possible confounding factors (e.g. sex, age, Sokal and ETLS scores, hemoglobin, platelets, leukocytosis, splenomegaly, type of treatment).

Statistical analyses will be carried out using Stata software (version 15, StataCorp, College Station) for a two-tailed type I error at 5% applying when appropriate a Sidak’s correction for multiple comparisons.

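### A 15-point difference in TKI intolerance is a hazard ratio of about 1.6 to 1.9, not 1.4; at 1.4 the 321 patients give roughly 39-48% power

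*Protocol article*

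**What the plan says.** The protocol article's Sample size section gives two calculations. The first, for biological age against frailty, leads to 200 patients and is not at issue. The second concerns tolerance to TKIs. It starts from the assumption that "it seems reasonable to expect 35% TKI intolerance" and concludes that "321 patients will enable us to identify a 15% absolute difference in intolerance (treated as censored data) for a two-sided type I error" of 5% with 80% power, "which correspond to a reasonable hazard ratio of at least 1.4".

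The section does not say whether 35% is the overall rate or the rate in one group, and it gives no group split for this comparison. The only split in the section belongs to the first calculation: "Considering 45% frail and pre-frail patients". The Data analysis section plans Cox-type models for tolerance and states that "The proportional hazards hypothesis will be tested using the Schoenfeld test and residual plot". Proportional hazards is therefore the article's own framework for linking a difference in proportions to a hazard ratio.

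**The concern.** The sentence presents 15 percentage points and a hazard ratio of 1.4 as the same effect on two scales. With an event rate near 35%, 1.4 looks too small for a 15-point gap. It is close to the risk ratio 50/35 = 1.43, which suggests that a risk ratio may have been labelled a hazard ratio. That origin is a guess; the mismatch does not depend on it.

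Tolerance is the main objective, and no other power statement covers it. Results from the Cox models will be on the hazard ratio scale. A reader comparing them with the Sample size section would take 1.4 as the smallest hazard ratio the study detects with 80% power, and could treat a non-significant result as evidence against an effect of that size.

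**Working it through.** **Inputs from the Sample size section:** N = 321, two-sided alpha 5%, power 80%, 15-point difference, 35% expected intolerance, hazard ratio (HR) 1.4.

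**Assumptions:** two groups, split 50:50, with 45:55 as a variant (the frail/pre-frail share from the first calculation); proportional hazards; rates are cumulative proportions over the same follow-up with no early loss. Three readings of the 35% are carried through: reference-group rate, overall rate, and the higher of the two rates.

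**1. Does 321 reproduce for 15 points?** Schoenfeld events = (1.960 + 0.842)² / [f(1−f)(ln HR)²], where f is the share in one group and (1.960 + 0.842)² = 7.849. N = events / mean event proportion.

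- 35% vs 50%: 139 events, N ≈ 326
- 27.5% vs 42.5% (35% overall): 107 events, N ≈ 304; Freedman's formula gives 112 events and N = 320
- 28.25% vs 43.25% (35% overall, 45:55): N ≈ 317

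So 321 is a reasonable figure for the 15-point target. Log-rank power with 321 patients is 79% for 35% vs 50% and 82% for 27.5% vs 42.5%.

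**2. What hazard ratio is 15 points?** HR = ln(1−p₁)/ln(1−p₀), with p₁ the higher rate.

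| Rates | Calculation | HR |
|---|---|---|
| 35% vs 50% | 0.693 / 0.431 | 1.61 |
| 27.5% vs 42.5% | 0.553 / 0.322 | 1.72 |
| 28.25% vs 43.25% | 0.567 / 0.332 | 1.71 |
| 20% vs 35% | 0.431 / 0.223 | 1.93 |

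None is near 1.4.

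**3. What difference can HR 1.4 give?** If S is the event-free proportion in the lower-risk group, the difference is S − S^1.4. It is largest where 1.4·S^0.4 = 1, so S = 0.431 and the difference is 0.123. Hence HR 1.4 never exceeds 12.3 points, whatever the rates or the split. From a 35% baseline it gives 1 − 0.65^1.4 = 45.3%, about 10 points.

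**4. Power of 321 patients at HR 1.4.** Power = Φ(√(E·f(1−f))·ln 1.4 − 1.960), with ln 1.4 = 0.3365 and E = 321 × mean event proportion. In each row the two rates differ by exactly HR 1.4, and f = 0.5.

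| Reading of 35% | Rates at HR 1.4 | Events | Power | N for 80% power |
|---|---|---|---|---|
| Reference rate | 35% vs 45.3% | 129 | 48% | about 690 |
| Overall rate | 30.3% vs 39.7% | 112 | 43% | about 790 |
| Higher rate | 26.5% vs 35% | 99 | 39% | about 900 |

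The last column is 7.849 / (0.25 × 0.1132) = 277 events divided by the mean event proportion. A 45:55 split lowers power by less than one point and raises the requirement to 280 events. Even with 136 events, the number expected under 35% vs 50%, power at HR 1.4 would be only 50%.

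**5. Hazard ratio detectable with 80% power.** HR = exp(2.802 / √(E·f(1−f))), with f = 0.5: 1.70 with 112 events and 1.62 with 136 events.

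**The case against.** The strongest reply is that the 80% power is attached to the 15-point difference, and 1.4 is only a trailing gloss. Since the wording is a lower bound, 1.61 to 1.93 satisfies it, so the sentence is loose rather than false. The first half stands: the design is not underpowered for its stated target. The second does not rescue the sentence. In a power statement, a minimum hazard ratio is read as the smallest one detectable at the stated power, and the text says the 15-point difference corresponds to it.

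A second reply is that 1.4 might be meant per standard deviation of a continuous biological-age measure. Power would then be about 95% with 112 events. But the article ties 1.4 to an absolute difference in intolerance and mentions no such scale.

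Third, the group split and the meaning of the 35% are not stated, so any single power figure at 1.4 rests on assumptions. This is right, and it is why a range is shown. The 12.3-point ceiling needs neither assumption, and more unequal groups would lower power further.

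Finally, this is an observational study, and reported confidence intervals will show what a null result excludes. That limits the harm but does not make the figure correct.

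**Conclusion.** The concern holds: the hazard ratio is wrong as written. A 15-point difference involving 35% implies a hazard ratio of 1.61 to 1.93, and 1.4 cannot yield 15 points at any baseline under proportional hazards. Power at 1.4 with 321 patients is about 39-48% across the readings of the 35%, assuming two near-equal groups and complete follow-up; early censoring would reduce it. The error lies in translating the effect scale. The sample size, alpha and 80% power are sound for the 15-point difference.

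**What to change.** Keep 321 and correct the sentence. The sponsor should state the two intolerance rates and the group split it used, then give the hazard ratio that follows. Possible wording: 321 patients (about 112 to 136 events) give about 80% power at two-sided 5% for a 15-point absolute difference (27.5% vs 42.5%, or 35% vs 50%), which corresponds to a hazard ratio of about 1.6 to 1.7. If the intended pair was 20% vs 35%, the hazard ratio is 1.93 and power about 87%, and the sentence should say so. Either delete 1.4 or add that power at that value is below 50% under the stated rates and split. Make the same correction in the full protocol and the analysis plan if they repeat the sentence.

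The cost is one corrected sentence and a less favourable stated detectable effect. No additional patients and no change to the analysis are needed.
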